Recently, a meta-analysis of five studies that investigated the effects of single-dose dexamethasone application prior to thyroidectomy demonstrated a significant reduction in the relative risk of PONV [30]. However, this meta-analysis was based on studies that did not control for factors potentially influencing PONV, such as postoperative opioid administration or the use of different anesthetics. Two of the five included studies enrolled exclusively Asian women [31,32]. Furthermore, serious doubts about the validity of one of the included studies have been expressed [33]. In summary, the generalizability of this meta-analysis is questionable, and further research is warranted to assess the true efficacy of a single, preoperative dose of dexamethasone for PONV prevention following thyroidectomy.

Recently, our group demonstrated that a bilateral superficial cervical plexus block during thyroid surgery under general anesthesia significantly reduced pain. Of even greater clinical importance, this block prevented the need for postoperative opioids [34,35]. Therefore, patients undergoing thyroidectomy and a bilateral superficial cervical plexus block are an ideal, homogenous cohort in which to investigate the efficacy of dexamethasone for postoperative PONV. These patients exhibit a high incidence of PONV and do not require opioids. They have no abdominal surgery that can cause nausea and vomiting via paralytic ileus. Combined with the highly standardized anesthesia protocol in use at our institution, this setting allows all known biases to be controlled.

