### Sample size calculation

A sample size determination was conducted for the main outcome variable, the incidence of PONV, using R environment version 13.2 with the gsDesign package. A preliminary retrospective analysis of 100 patients revealed a total incidence of PONV of 48% (unpublished data), confirming previous studies [39]. Based on a power of 0.80 (p = 0.05, two-sided) to detect a 50% reduction in the incidence in PONV (48% vs. 24%) as the clinically relevant treatment advantage between two balanced arms, a total of 123 patients were required for a fixed design. To account for deviations from the expected effect size and incidence due to the avoidance of opioids for postoperative pain relief, a group sequential design was implemented with one interim analysis after 70 patients have completed the study treatment. In a symmetric, two-sided group sequential design with an O’Brien-Flemming alpha spending function [40], the inflation factor was 1.006. The adjusted sample size was estimated to be a total of 124 patients (62 patients per arm). With an assumed rate of 18% protocol violations (derived from a preliminary retrospective analysis of 100 patients), the calculated total sample size was 152 patients (76 patients per arm). To recruit this number of patients, a 30-month inclusion period was anticipated.

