### Randomization: sequence generation, allocation concealment mechanism and implementation

The randomization will be 1:1 for each arm without stratification. Treatment allocation will be performed according to predefined block randomization list with random block sizes between four and ten. Only the data manager (UB) has access to this computer generated randomization list. Two to three days before surgery the data manager will prepare a computer generated study medication request form based on the patient’s study number. The request contains the patient’s name and the treatment allocation. The form will be placed in an opaque, sealed and signed envelope and will be directly delivered to the pharmacy by study personnel. Study medication will be prepared according to the request form by the hospital pharmacy as described earlier and will be delivered to the anesthesiologist by an assigned surgical resident.

If the allocated study treatment planned cannot be performed, the patient will remain on the study and will be included in the intention-to-treat (ITT) analysis. An explanation for the non-adherence must be supplied.

In case of an emergency two principal investigators (TC, IT) and the data manager can break the blinding of single patients. Unblinding is computer-based and is only available if the principal investigators are signed-in as users. Before unblinding a reason for unblinding has to be given. For each unblinding, the reason, the requestor, the computer ID, the time and date are recorded. The data manager will be automatically informed in case of an unblinding.

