### Statistical analysis

The statistical analysis will be performed with SAS 9.1 (SAS Institute Inc., Cary, NC, USA). Missing values will be replaced with the last available value (the last observation carried forward approach, LOCF). For the baseline characteristics, descriptive statistics will be used as appropriate.

Two analyses (interims analysis and final analysis) will be performed for the primary outcome. To maintain the alpha, an O’Brien-Flemming alpha spending function [40] will be used. The alpha values used for the primary outcome will be 0.0039 in the interim analysis and 0.0488 in the final analysis. Both alphas will be adjusted for the exact proportion of information included in the interim analysis if the analysis is not performed for exactly 70 patients. For all other analyses, two-sided significance tests with an alpha of 0.05 will be applied.

All confirmatory analyses will be performed primarily as ITT analyses; the available data from all the patients will be assessed for the outcomes according to the randomization. To assess the treatment effects of dexamethasone vs. placebo in patients with no postoperative use of opioids, additional analyses will be conducted excluding the patients with protocol violations.

For the superiority analysis of dexamethasone vs. placebo in terms of the incidence of PONV (the primary outcome), a chi-square statistic will be applied. Mixed models assessing the mean ranks of the scores with adjustments for time and treatment vs. time interactions will be applied to analyze the following secondary outcomes: the severity of PONV, the intensity of pain at rest and the intensity of pain under provocation. The Mann–Whitney U statistic will be used to assess the following secondary outcomes: the required amount of anesthetic medication, the amount and type of postoperatively administered analgesics and the length of hospital stay. Postoperative morbidity and wound healing at the time of discharge and six weeks after the intervention will be assessed using a chi-square statistic.

Auxiliary, non-confirmatory analyses will be performed to assess the influences of baseline and treatment characteristics on the primary and secondary outcomes.

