We would like to acknowledge the potential limitations of this study protocol. First, although the scale for PONV measurement has been previously used it is not an explicitly validated scale. Nevertheless, as only patients vomiting or receiving antiemetic medication will be considered to suffer PONV the bias resulting from subjective ratings should be minimal. Second, recent studies suggested that 5-HT3 receptor antagonists might be more effective than dexamethasone in preventing postoperative nausea and vomiting [43]. Nevertheless, in times of constant pressure on health care expenses, the low cost and the general availability of dexamethasone still make it a relevant option for prevention of PONV. Third, although no opioids are applied in the postoperative course they are unavoidable during general anesthesia. Thus it could be possible that differences in operation time might lead to a different amount of applied remifentanil, potentially leading to a bias in PONV. As the study is randomized we consider such a bias very unlikely. However, since we record the amount of applied fentanyl and remifentanil, in case of an imbalance we will be able to adjust for this bias. Fourth, for pain measurement we will use a Verbal Rating Scale ranging from 0 to 10 instead of a 100 mm Visual Analog Scale. At our institution the use of this Verbal Rating Scale for pain measurement during the postoperative course is a common and well established clinical routine. Furthermore, patients are preoperatively informed to rate their pain using the Verbal Rating Scale.

In the present project, we reduced bias as much as possible. Thus, we expect to definitively clarify the efficacy of dexamethasone for PONV prophylaxis. The confirmation of this efficacy by our study will have a major impact because the results may establish dexamethasone administration before thyroidectomy as a new standard in clinical practice. Moreover, the results of this study could be applicable to all types of operations that involve general anesthesia and will stimulate further clinical research in this area.

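### The primary chi-square is valid but uses no baseline information; a cheap gain is available, and the one named bias adjustment relies on opioid amounts that arise after the study drug

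*Protocol article*

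**What the plan says.** Four statements in the protocol article bear on this.

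- Randomization section: "The randomization will be 1:1 for each arm without stratification".
- Statistical analysis, primary outcome: "For the superiority analysis of dexamethasone vs. placebo in terms of the incidence of PONV (the primary outcome), a chi-square statistic will be applied". The alphas are 0.0039 at the interim and 0.0488 at the final analysis.
- Statistical analysis, last paragraph: auxiliary, non-confirmatory analyses will "assess the influences of baseline and treatment characteristics on the primary and secondary outcomes".
- Discussion, third limitation: longer operations could mean more remifentanil. The amounts of fentanyl and remifentanil are recorded, so "in case of an imbalance we will be able to adjust for this bias".

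Two other sections matter. Intervention/treatment places the study drug 30 to 60 minutes before incision, with anaesthesia following it. Outcome measurements lists the total fentanyl and remifentanil amounts as a secondary outcome, which Statistical analysis tests with the Mann–Whitney statistic.

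**The concern.** Age, sex and scheduled extent of surgery (partial or total) are known for every patient before randomisation, yet none enters the stratification or the confirmatory test. If any of them predicts nausea and vomiting, the unadjusted comparison gives up some precision, and a chance imbalance shifts the observed difference.

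The one adjustment that the article explicitly offers as a cure for bias uses a variable of the wrong kind. Opioid amounts are determined after the study drug is given, and the article treats them as a possible drug effect in one place and as a nuisance factor in another. The adjustment would be made only if an imbalance is seen. A result adjusted in this way could be read as a correction of the primary result when it may be the more biased of the two.

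**Working it through.** **1. Plan's own sample size.** Inputs from Sample size calculation: 48% vs 24%, two-sided 0.05, power 0.80. With pooled rate 0.36 and no continuity correction, the total is

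2 × [1.96 × √(2 × 0.36 × 0.64) + 0.842 × √(0.48 × 0.52 + 0.24 × 0.76)]² / 0.24² = 123.2.

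This agrees with "a total of 123 patients were required for a fixed design". Then 123.2 × 1.006 = 123.9, so 124; and 124 / 0.82 = 151.2, so 152 in two equal arms. The planned test and the planned size agree.

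**2. Validity of the chi-square.** Exact enumeration at alpha 0.0488, taking the final look alone:

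| Per arm | Type I error (48% in both arms) | Power (48% vs 24%) |
|---|---|---|
| 62 | 0.059 | 0.806 |
| 76 | 0.044 | 0.880 |

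The departures from 0.0488 come from discreteness.

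**3. What baseline information could add.** The article gives no prognostic strengths. Assumed: 80% women with odds ratio 2 to 3; half total thyroidectomy with odds ratio 1.5 to 2; age odds ratio 1.2 to 1.5 per SD. A score test of treatment in a logistic model with these three covariates gains about 0 to 3 power points over the chi-square. With a single, stronger baseline score (odds ratio 1.5 to 3 per SD), a logistic model reaches 0.81 to 0.86 at 62 per arm and 0.88 to 0.93 at 76 per arm, a gain of about 0 to 5 points on the exact figures above.

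**4. Size of a chance imbalance in sex.** With 80% women, the 95% limit is 1.96 × √(2 × 0.8 × 0.2 / n).

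- n = 62: 0.141, about 14 points.
- n = 76: 0.127, about 13 points.

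At odds ratio 3 and 48% overall, the risk gap between women and men is about 0.257. The observed difference would move by 0.141 × 0.257 = 0.036, or 0.127 × 0.257 = 0.033, against a planned difference of 0.24. This pairs a limit of the 95% range with the top odds ratio.

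**5. Which adjusted test holds its alpha.** Under the assumptions of step 3, null rejection rates are:

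| Test | 70 patients, alpha 0.0039 | 152 patients, alpha 0.0488 |
|---|---|---|
| Wald test of standardised risk difference | 0.009–0.010 | 0.058–0.059 |
| Score test, same logistic model | 0.004–0.005 | 0.051–0.053 |

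The Wald version more than doubles the interim alpha. The score test stays near nominal.

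**6. Adjusting for opioid amount.** Simulation with 76 per arm. Neither drug nor dose affects nausea and vomiting. Where a shared cause is present, it has correlation 0.6 with dose and log odds 1.0 per SD on the outcome. The model contains treatment and dose, tested at alpha 0.0488.

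| Drug lowers dose by | Shared unmeasured cause | Adjusted odds ratio | Rejection |
|---|---|---|---|
| 0 | no | 1.00 | 0.044 |
| 0 | yes | 1.01 | 0.048 |
| 0.25 SD | no | 1.00 | 0.046 |
| 0.25 SD | yes | 1.14 | 0.072 |
| 0.5 SD | no | 1.01 | 0.051 |
| 0.5 SD | yes | 1.31 | 0.109 |

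Bias needs both conditions. The second is plausible: Intervention/treatment has remifentanil titrated to the patient's haemodynamics and movement. The first is open, and the trial itself tests it as a secondary outcome.

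**The case against.** The strongest reply is that nothing here is wrong. Unstratified randomisation, an unadjusted sample size and an unadjusted test fit together, and the type I error of the test already allows for chance imbalance. That stands, and it limits the point to an improvement.

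Three stronger readings are tempting, and the article does not support them.

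- *That the opioid adjustment is the only one foreseen.* It is not. Baseline characteristics are to be examined in auxiliary analyses. That the article names no covariates for these is no fault, since such detail can sit in an analysis plan that is not shown.
- *That the trial breaks its own standard because it faults earlier studies that* "did not control for factors potentially influencing PONV". The sentence goes on to give postoperative opioids and differing anaesthetics as examples. The trial deals with those by design, through the cervical block, the standardised anaesthetic and an additional analysis without protocol violators. It is not a complaint about missing covariate adjustment.
- *That the dose adjustment biases the primary result.* It is a contingency in the Discussion and leaves the primary test untouched. Dose is also a treatment characteristic, so the auxiliary analyses that the plan calls non-confirmatory may already cover it. Still, the Discussion presents the adjustment as able to remove bias, and that claim needs correcting.

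Two further objections change the remedy. A Wald test of the standardised risk difference at the stated alphas would be anti-conservative (step 5). And extent of surgery as performed is settled after the study drug, so only the planned extent qualifies as baseline. Finally, the article reports recruitment as ongoing, so changing the primary test is more than a wording edit.

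**Conclusion.** A low-cost improvement, not an error. The chi-square is valid and properly sized. Ignoring baseline factors costs about 0 to 3 power points, from an unadjusted 0.81 at 124 patients or 0.88 at 152. That figure rests wholly on assumed prognostic strengths; if sex, age and extent of surgery predict little, the gain is nil.

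The opioid-dose adjustment is the weaker part of the plan. It is triggered by the data, uses a variable arising after the study drug, and treats a secondary outcome as a confounder. Whether it would mislead depends on two conditions that the article cannot settle: that dexamethasone changes the dose, and that dose and nausea or vomiting share a cause. If both hold at the assumed strengths, a null effect appears as an odds ratio of 1.14 to 1.31. If either fails, there is no material bias.

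**What to change.** Before unblinding, including the coded interim look:

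1. Test the treatment effect with a score test from a logistic model containing treatment, sex, age and planned (not performed) extent of surgery, at the stated interim and final alphas. Report the standardised risk difference from that model as the estimate, without basing the test on its Wald statistic. Keep the chi-square as a sensitivity analysis.
2. If the primary test cannot be changed now that recruitment is under way, keep the chi-square as primary and prespecify this model as the named sensitivity analysis.
3. Replace the Discussion's imbalance-triggered adjustment with a statement that any result adjusted for fentanyl or remifentanil amount is exploratory and does not correct the primary result.

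Cost: a slightly more complex analysis that must be fixed in advance. If the primary test changes, the change has to be documented while the trial is running. Sample size and visits stay the same, and the covariates are already known at enrolment.

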### Blinding

The patients, all personnel involved in patient care or treatment, the data collectors, and the outcome adjudicators will be blind to the treatment allocation. Only the data manager of the trial, who is not involved in the treatment or patient care, has access to the treatment allocations. For the interim analysis the statistician will be provided with non-descriptive arm assignments (A, B). If the trial chairperson or co-chairperson decides that the occurrence of AEs or SAEs necessitates un-blinding, the data manager of the trial will reveal the treatment allocation of that patient.

### Ethical issues

This protocol, the patient information sheet and the patient consent form have been reviewed and approved by the local Ethics Committee of the Canton St. Gallen (EKSG10/082/2B) and by Swissmedic (2011DR3005) prior to enrolling any patients in this trial. All the patients will be informed about the aims and procedures of the trial, possible adverse events, how to react if an adverse event occurs and possible hazards to which they may be exposed. The participants will be informed that their patient data will be held strictly confidential but that that their medical records may be reviewed for trial purposes by authorized individuals other than their treating physician. It will be emphasized that participation is voluntary and that the patients are allowed to refuse further participation in the trial whenever they want. Data obtained prior to the withdrawal of the patient will be included in the analysis. Written informed consent will be required for all the patients entering the trial. Two copies of the consent form must be signed, one of which will be retained by the patient. The clinical investigator who enters the patient into the trial is responsible for obtaining informed consent.

## Discussion

The present study investigating the efficacy of a single, preoperative dose of dexamethasone for PONV in patients undergoing thyroidectomy will be the first in the literature to explicitly control for all known sources of bias. The setting proposed in the present protocol is ideal for several reasons. First, patients undergoing thyroidectomy have a high incidence of PONV [2,12,13]. Therefore, these patients are ideal subjects for testing new antiemetic strategies because the study will unlikely be underpowered and the patients will not be unnecessarily exposed to the inherent risks. Second, the included patients do not undergo abdominal surgery, which can cause a postoperative paralytic ileus that can also provoke nausea and vomiting [42]. In such a confounding setting, accurately differentiating between the nausea and vomiting caused by the anesthesia and that caused by the operation itself would be impossible. Third, through the application of the cervical block, postoperative opioids should not be needed by the majority of the patients [35]. As well-known causes of nausea and vomiting, opioids might also confound the analysis of the efficacy of dexamethasone for preventing PONV [42]. Although prohibiting the use of opioids in the present study would have been ideal, it is not possible for ethical reasons. Therefore, opioid administration, if necessary, is defined as an exclusion criterion. A difficulty arises from the allocation of patients to a specific arm (active drug vs. placebo) prior to any decision to administer the opioid medication; therefore, patients receiving opioids cannot be excluded from the ITT analysis. As a consequence, the per-protocol analysis will be critically important for evaluating the true efficacy of dexamethasone in preventing PONV. Fourth, all the patients will receive the same standardized anesthesia protocol, which will be crucial for avoiding sources of bias that were not considered in previous studies [30].

We would like to acknowledge the potential limitations of this study protocol. First, although the scale for PONV measurement has been previously used it is not an explicitly validated scale. Nevertheless, as only patients vomiting or receiving antiemetic medication will be considered to suffer PONV the bias resulting from subjective ratings should be minimal. Second, recent studies suggested that 5-HT3 receptor antagonists might be more effective than dexamethasone in preventing postoperative nausea and vomiting [43]. Nevertheless, in times of constant pressure on health care expenses, the low cost and the general availability of dexamethasone still make it a relevant option for prevention of PONV. Third, although no opioids are applied in the postoperative course they are unavoidable during general anesthesia. Thus it could be possible that differences in operation time might lead to a different amount of applied remifentanil, potentially leading to a bias in PONV. As the study is randomized we consider such a bias very unlikely. However, since we record the amount of applied fentanyl and remifentanil, in case of an imbalance we will be able to adjust for this bias. Fourth, for pain measurement we will use a Verbal Rating Scale ranging from 0 to 10 instead of a 100 mm Visual Analog Scale. At our institution the use of this Verbal Rating Scale for pain measurement during the postoperative course is a common and well established clinical routine. Furthermore, patients are preoperatively informed to rate their pain using the Verbal Rating Scale.

In the present project, we reduced bias as much as possible. Thus, we expect to definitively clarify the efficacy of dexamethasone for PONV prophylaxis. The confirmation of this efficacy by our study will have a major impact because the results may establish dexamethasone administration before thyroidectomy as a new standard in clinical practice. Moreover, the results of this study could be applicable to all types of operations that involve general anesthesia and will stimulate further clinical research in this area.

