### Intervention/treatment

Study medication will be prepared by the hospital pharmacy. Medication will be delivered in a syringe containing either 2 ml saline (placebo) or 2 ml saline with 8 mg dexamethasone (Mephameson®, Mepha Pharma, Basel, Switzerland) and are indistinguishable. Syringes will be labeled with the patient’s name, the study name and the study’s patient number.

The anesthesiologist will administer the study medication intravenously 30–60 min before surgery (skin incision) and is completely unaware of the treatment allocation. Thereafter, all the patients will undergo standardized anesthesia, thyroid surgery and routine postoperative care. During the surgery, recurrent laryngeal nerve monitoring will be performed.

A bilateral superficial cervical plexus block will be performed just before the skin incision with a 20-ml syringe and a 20-G × 2^3^/_4_-inch needle (total dose, 20 ml). On each side of the neck, 10 ml of 0.5% bupivacaine solution (Carbostesin® 0.5%; AstraZeneca, Zug, Switzerland) will be administered (total dose, 20 ml) according to the following procedure. On the first side of the neck, along the cranial dorsal edge of the sternocleidomastoid muscle, three deposits of approximately 2.5 ml each will be injected to anesthetize the cervical plexus and its *nervus transversus colli*. To anesthetize the region of the planned skin incision, the remaining 2.5 ml will be injected subcutaneously on each side of the incision. The same procedure will be performed on the opposite side of the neck, using the remaining 10 ml of bupivacaine solution.

The anesthestic technique will be standardized using propofol (Disoprivan® 1%; AstraZeneca) for hypnosis, fentanyl (Sintenyl®, Sintetica, Mendrisio, Switzerland) and remifentanil (Ultiva®;GlaxoSmithKline, Münchenbuchsee, Switzerland) for analgesia, and rocuronium (Esmeron®, MSD, Lucerne, Switzerland) for muscle relaxation.

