Propofol will be used as total intravenous anesthesia in a target-controlled infusion (TCI) system according to the Schnider model [37]. Induction will be performed with propofol at an effect-site concentration (Ce) of 4 μg/ml and will be maintained at a Ce of 2–2.5 μg/ml to hold the bispectral index value between 40 and 60. Analgesia will be performed with 0.3-0.4 mg of fentanyl administered intravenously at the beginning of anesthesia. Anaesthesia will be supplemented by remifentanil allowing for stable hemodynamics and avoidance of movements. Remifentanil will be administered in a TCI system according to the Minto model [38], beginning with a Ce of 2–3 ng/ml and increasing to 10–12 ng/ml at the end of anesthesia. Tracheal intubation will be facilitated with intravenous rocuronium at 0.5 mg/kg bodyweight. No further relaxation will be induced because of intraoperative recurrent laryngeal nerve monitoring.

The postoperative first-line therapy for PONV will be intravenous droperidolum (Droperidol®, Sintetica, Mendrisio, Switzerland), with a maximal dose of 3 × 0.5 mg/24 h if the patient’s blood pressure exceeds 120 mmHg. The second-line therapy will be ondansetron (Zofran®, GlaxoSmithKline, Münchenbuchsee, Switzerland) at a dose of 4 mg intravenously.

No routine analgesia is planned. The first-line reserve for pain relief on patient demand will be 1 g of paracetamol (Dafalgan®; Bristol-Myers Squibb, Baar, Switzerland) administered by mouth, with a maximal dose of 3 g/24 h. The second-line reserve will be 1 g of metamizole (Novalgin®; Sanofi-Aventis, Meyrin, Switzerland), with a maximal dose of 4 g/24 h. The third-line reserve will be intravenous morphine (Morphin HCI®, Sintetica, Mendrision, Switzerland); however, its necessity will constitute a protocol violation.

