### Outcome measurements

The primary outcome will be the incidence of PONV, which will be assessed at postoperative hours 4, 8, 16, 24, 32 and 48. A patient will be considered to suffer from PONV if nausea or vomiting is documented at any of the postoperative assessments.

One secondary outcome will be the severity of the PONV, measured with a score ranging from 0 to 3 (0 for no nausea; 1 for mild nausea, defined as nausea requiring a single administration of an antiemetic drug; 2 for severe nausea, defined as nausea requiring the repeated administration of antiemetic drugs; and 3 for nausea leading to vomiting).

Other secondary outcomes will be the intensity of pain at rest and under provocation (while rotating the neck 90° to each side), measured at postoperative hours 4, 8, 16, 24, 32 and 48 with a Verbal Rating Scale (VRS) ranging from 0 to 10, with 0 considered to be no pain and 10 considered to be the worst pain imaginable. Additional secondary outcomes will include the length of hospital stay (measured as the number of hours after the intervention), wound healing at the time of discharge and six weeks after the intervention, the amount of anesthetic medication required (total amount of administered fentanyl, remifentanil, rocuronium measured in mg and the total amount of administered remifentanil measured in μg) and postoperative in-hospital morbidity, including wound infection, reoperation, bleeding, prolonged intubation, laryngeal nerve lesion, urinary retention, urinary tract infection, pulmonary infection and gastrointestinal hemorrhage or newly occurring insulin dependence in diabetic patients.

For the safety analysis, adverse events (AEs) and serious adverse events (SAEs) will be evaluated. The patients will be instructed by the investigator to report the occurrence of any AE, defined as an unfavorable and unintended sign, symptom or disease temporally associated with the treatment provided in the present trial. The investigator (treating physician) will be asked to verify the absence or presence of all the AEs predefined on the CRF. Information in the patients’ medical files will be reported using the Common Terminology Criteria for Adverse Events v4.03 (CTCAE 4.03) coding system, rather than a narrative description. AEs will be scored as grade 1 (a mild AE) to grade 5 (death related to the AE), and a causality assessment will be performed.

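### The Discussion leaves open a data-triggered adjustment of the PONV comparison for intraoperative opioid amounts, which arise after the study drug and are themselves a secondary outcome

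*Protocol article*

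**What the plan says.** All places are in the protocol article.

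- **Intervention/treatment.** The study drug is injected 30 to 60 minutes before skin incision. "Thereafter, all the patients will undergo standardized anesthesia, thyroid surgery and routine postoperative care". Fentanyl is "0.3-0.4 mg of fentanyl administered intravenously at the beginning of anesthesia". For remifentanil: "Anaesthesia will be supplemented by remifentanil allowing for stable hemodynamics and avoidance of movements".
- **Outcome measurements.** The secondary outcomes include "the amount of anesthetic medication required", and fentanyl and remifentanil are named in it.
- **Statistical analysis.** PONV incidence is compared by chi-square, with confirmatory analyses primarily by intention to treat. The amount of anesthetic medication is compared between arms by Mann–Whitney U. Analyses of baseline and treatment characteristics are classed as auxiliary and non-confirmatory.
- **Discussion, limitations.** The authors note that "differences in operation time might lead to a different amount of applied remifentanil, potentially leading to a bias in PONV". They consider this very unlikely because the trial is randomised, and add: "since we record the amount of applied fentanyl and remifentanil, in case of an imbalance we will be able to adjust for this bias".
- **Aim of the study.** The objective is the preventive benefit of a single preoperative dose.

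**The concern.** The article gives one variable two roles. In the outcome and analysis sections, opioid amount is something dexamethasone may change. In the Discussion, a difference in it is a bias to be removed from the effect of dexamethasone.

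Randomisation fixes the comparison at the time of allocation. Opioid amount is determined later, and remifentanil is titrated to the patient's response under anesthesia. If dexamethasone lowers opioid need, and opioids provoke PONV as the Discussion itself states, then lower opioid use is one route by which the drug works. Conditioning on it removes that route and leaves a partial effect, which is not the effect named in the aim. It can also introduce distortion through causes shared by opioid amount and PONV, such as a difficult operation.

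Operating time, the cause the Discussion has in mind, is also known only after randomisation. The trigger has no threshold, so whether the adjusted model is used would depend on the observed data.

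**Working it through.** **1. The plan's own figures.** Inputs from Sample size calculation: 48% vs 24%, two-sided 0.05, power 0.80, inflation factor 1.006, 18% protocol violations. With pooled variance and no continuity correction:

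n per arm = [1.960 × √(2 × 0.36 × 0.64) + 0.8416 × √(0.48 × 0.52 + 0.24 × 0.76)]² / 0.24² = (1.3305 + 0.5532)² / 0.0576 = 61.6

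- Total 123.2 (plan: 123).
- 123.2 × 1.006 = 123.9, so 124 (plan: 124).
- 124 / 0.82 = 151.2, so 152 in equal arms (plan: 152).

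The figures reproduce. At the final alpha of 0.0488, the unadjusted chi-square test has 80.0% power with 62 per arm and 87.5% with 76 per arm. This point does not change the sample size.

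**2. Order of events.** Study drug, then anesthesia with titrated remifentanil, then total opioid amount, then PONV over 48 hours. Opioid amount lies after treatment and before outcome, so it cannot confound the randomised comparison. It can only carry part of the effect or differ by chance.

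**3. What adjustment would do, on assumed values.** The documents give neither the effect of dexamethasone on intraoperative opioid amount nor the slope of PONV on that amount. Let T = 1 for dexamethasone and M be opioid amount in SD units:

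- M ~ Normal(−δT, 1)
- logit P(PONV) = a + bT + γM

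For each δ and γ, a and b are solved so that the overall risks are 48% and 24%. The adjusted difference is the risk at T = 0 minus the risk at T = 1, each averaged over M in both arms combined. For δ = 0.5 and γ = 0.5, a = −0.085 and b = −0.880. The standardised risks are 45.1% and 26.3%, a difference of 18.8 points.

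Power is from 10,000 simulated trials per row, 76 per arm, alpha 0.0488, γ = 0.5. The adjusted test is the Wald test of T in a logistic model with M.

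| Opioid amount on dexamethasone | Adjusted difference (points) | Share of 24 points removed | Power, unadjusted chi-square | Power, adjusted |
|---|---|---|---|---|
| no change | 24.0 | 0% | 88% | 89% |
| 0.1 SD lower | 23.0 | 4% | 88% | 86% |
| 0.25 SD lower | 21.4 | 11% | 88% | 80% |
| 0.5 SD lower | 18.8 | 22% | 88% | 67% |

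Smaller simulations of the same model gave 78% to 81% adjusted power for the 0.25 SD row and 66% to 69% for the 0.5 SD row. The second digit should not be over-read.

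**4. Sensitivity to the slope.** With opioid amount 0.5 SD lower, the adjusted difference is 19.8 points at γ = 0.4, 17.0 at 0.7 and 16.1 at 0.8. With no drug effect on opioid amount it is 24.0 points at every slope.

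**The case against.** The strongest reply is that the analysis section already settles the matter. It fixes an unadjusted chi-square test by intention to treat. Intraoperative opioid amount is naturally read as a treatment characteristic, so any analysis using it would be auxiliary and non-confirmatory. The Discussion speaks only of being able to adjust, in a limitations paragraph, for a bias it thinks very unlikely. This stands. A reader might infer that the plan would adjust its primary comparison, or that the trial's power would fall from 88% to 67%. Neither follows: no section lets an adjusted result replace the chi-square test, and the lower power belongs to a test that is not confirmatory.

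A second reply is that the mechanism is assumed. The Background credits corticosteroids with reducing postoperative pain and says nothing of intraoperative opioid need. Fentanyl is given within a narrow range at the start, every patient has the cervical block, and the anesthesiologist is blinded. This also stands. The exposure is mainly through remifentanil, and if an imbalance is pure chance, adjustment removes none of the effect.

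What remains is that the sentence calls such a difference a bias and offers adjustment as its correction, without separating a chance difference from one caused by the drug. Observed data cannot reliably tell the two apart, and in the second case the correction is wrong.

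**Conclusion.** The point holds as a minor one. The Discussion leaves open a data-dependent adjustment for a post-randomisation variable that the plan also tests as an outcome, and presents it as a bias correction. If dexamethasone changes opioid need, the adjusted figure does not estimate the total effect of one preoperative dose, and reporting it as the corrected result would mislead.

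On the assumed values, the loss runs from nothing (no opioid-sparing effect) to 4.2 to 7.9 of the 24 points (0.5 SD sparing, slopes 0.4 to 0.8). These figures illustrate the mechanism; they do not predict what dexamethasone does. The primary test, its alpha and the sample size are unaffected.

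**What to change.** Replace the sentence on adjusting for opioid imbalance with a statement that:

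- the PONV treatment effect is not adjusted for intraoperative opioid amount or operating time, whatever imbalance is seen;
- opioid amounts are reported by arm as the planned secondary outcome, and operating time descriptively;
- any adjusted sensitivity analysis uses only pre-randomisation covariates, chosen in advance and applied regardless of observed balance;
- any opioid-adjusted result is labelled exploratory (mediation) and does not replace the chi-square analysis in the Statistical analysis section.

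This leaves room for a labelled exploratory analysis. The cost is a few lines of text, with no further patients and no change to the primary analysis. Operating time, which the article does not list as a recorded item, would need to be available for the descriptive comparison.
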